## Materials and methods

### Study design

This is a double-blinded, double-dummy, and placebo-controlled trial with three parallel groups. The protocol design was based on the recommendations made in the 'Design of Treatment Trial for Functional Gastrointestinal Disorders’, as proposed by the Rome III Working Team [3] and the Consolidated Standards of Reporting Trials (CONSORT) statement [18]. Two hundred and ninety-one participants were recruited from Lee Kee Memorial Dispensary (General outpatient clinic), Li Ka Shing Specialist Clinic of Prince of Wales Hospital and clinics of the School of Chinese Medicine, Hong Kong Baptist University. After a 2-week run-in period, eligible subjects were randomly assigned to one of three arms, the Chinese medicine (CHM) arm, the western medicine (WM) arm, and the placebo arm. The CHM arm received MZRW and WM placebo, the WM arm received senna and the CHM placebo, and the placebo arm received the CHM placebo and the WM placebo. All three groups then underwent an 8-week treatment and an 8-week follow-up period. Five visits in total were scheduled for each subject: one visit each in week 0, week 2, week 4, week 8 and week 16. The participant flowchart is listed in Figure 1 and the participant timeline is listed in Figure 2. The study protocol was approved by the Hong Kong Baptist University Ethics Committee on the Use of Human Subjects for Teaching and Research (Approval no. HASC/10-11/16) and the Joint Chinese University of Hong Kong-New Territories East Cluster Clinical Research Ethics Committee (Approval no. CRE-2013.192-T).

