### Outcomes

Participants recorded stool frequency, stool form (on the 7-point Bristol stool scale, ranging from 'Separate hard lumps’ to 'Watery’), and feeling of complete evacuation (yes/no). They were also required to log intake of research medication, rescue drug and/or any other medication use throughout the study in a daily diary. Principal investigators (PIs) and research assistants (RAs) interviewed patients at the end of Week 2 (baseline), Week 4 (within treatment), Week 8 (end of treatment), and Week 16 (end of follow-up), for symptoms, compliance, and occurrence of adverse events. Data on global symptom improvement, individual bowel symptoms and stool consistency were collected.

Individual assessment of constipation and related symptoms (severity of constipation, sensation of straining, incomplete evacuation, bloating, abdominal pain/cramping, nausea and passing of gas) were recorded using a 7-point ordinal scale (0 = not at all, 6 = very severe) [see Additional file 2: Table S1] on a designated form that participants filled out during every visit [3]. Global symptom improvement was defined as the participant's subjective feeling of adequate relief of symptoms. For this purpose, participants were asked to rate their impression of changes in constipation by scoring (in comparison with their baseline (Week 2) scores) their impression of these changes from 0 to 6 to represent that they were feeling markedly worse or better at the respective extremes [3]. The response categories are collapsed to simply 'Improved’ for score 4 to 6, 'Same’ for score 3 or 'Worse’ for score 0 to 2 [24].

The primary outcome will be the response rate for CSBM during the treatment period: a clinically meaningful endpoint that combines an objective measure (number of bowel movement) with a subjective measure (feelings of patients as to completeness of defecation) [25,26]. Participants with a mean increase of CSBM ≧1/week compared with the last 14 days of the run-in period are defined as responders.

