Secondary outcomes will include the response rate for CSBM during the follow-up period, including stool frequency, changes from baseline in scores of individual symptom assessment (severity of constipation, sensation of straining, incomplete evacuation, bloating, cramping/abdominal pain, nausea and passing of gas), and global symptom assessment (improved, same or worse). Safety profiles of MZRW will be assessed by determining important adverse events reported in participants’ diaries, in follow-up interviews and in clinical laboratory evaluations (for example, liver and renal function testing). During the last visit, the success of blinding would be evaluated for both investigators and patients, as to whether CHM, WM or placebo had been taken. In particular, patients are asked to rate the appearance, color, texture, taste and efficacy of the medication to try to determine whether these factors were important in their conclusion.

In addition, an objective estimate of changes in colonic transit time is made based on a commercially available radio-opaque Sitzmarks capsule (Konsyl Pharmaceuticals, INC.,Easton, MD 21601,U.S.A).

Each gelatin capsule contains 24 barium sulfate embedded polyvinyl chloride markers measuring 1 mm × 4.5 mm. Plain radiographs of the abdomen are obtained after patients swallow a capsule, for five days (120 hours) before and 8 weeks after the treatment period. Normal colonic transit is defined as expulsion of at least 80% (19 or more) markers [27,28]. For patients with six or more makers scattered throughout the colon, hypomotility or colonic inertia is suggested. If six or more markers are gathered in the rectosigmoid region with a near normal transit of markers through the rest of the colon, functional obstructive or dys-synergic defecation is suspected [4,29].

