### Sample size calculation

From the results of the placebo-control study, the response rate of MZRW was 43.3% [14]. Assuming the response rates for TCM, senna and placebo were 40%, 20% and 10%, respectively. Therefore, 82 patients per treatment group were deemed sufficient to achieve 80% power in detecting treatment differences, based on two-sided Chi-square test without continuity correction at a significance level of 0.025 (used to maintain the overall significance level at 5%). Further, assuming a 15% dropout rate, we concluded that a total of 291 patients (97 per arm) would need to be recruited to ensure statistically significant results. The calculation is performed using StudySize 2.0 software, London, UK.

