### Statistical analysis

All efficacy and safety analyses will be conducted according to the intention-to-treat (ITT) principle. Missing values will be imputed by the last-observation-carried-forward method. The statistical analysis will be performed using the Statistical Packages of Social Sciences (SPSS) for Windows version 16.0. The statistical significance is defined as two-sided *P* value of <0.05. Baseline characteristics will be reported as mean (SD). Baseline differences among the groups will be assessed with the use of Student’s t-test for normally distributed continuous variables and the non-parametric Mann-Whitney U test for non-normally distributed variables. For categorical variables, chi-squared test or Fisher’s exact test will be used. Comparisons between groups will be conducted by using an analysis of covariance (ANCOVA) with baseline as covariate. All items and subscales will be compared between groups for each 6-week treatment using ANCOVA, with treatment group as a factor in the model and baseline as the covariate. The changes from baseline to endpoint of treatment in scores will be tested with repeated measure analysis of variance (ANOVA). Within group differences will be assessed with paired t-test for normally distributed data and Wilcoxon signed-rank test for non-normally distributed data.

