The trial would be terminated in a specific subject if he/she has: 1) presence of severe adverse effect; 2) hypersensitivity towards research medication; 3) participation in another CHM research project; or 4) presence of life-threatening disease. The whole research plan would be terminated for the following circumstances: 1) presence of serious adverse effect related to the research medication with supportive evidence; or 2) completion of all follow-up assessments.

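### Unrestricted last-observation-carried-forward fills the off-drug follow-up responder rate with on-drug data and lets early leavers count as primary responders on short records

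*Protocol article*

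**What the plan says.** The Statistical analysis section of the protocol article sets the analysis set and the missing-data rule in consecutive sentences: "All efficacy and safety analyses will be conducted according to the intention-to-treat (ITT) principle", then "Missing values will be imputed by the last-observation-carried-forward method". Neither sentence excepts any endpoint or period.

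The Outcomes section defines two responder endpoints.
- Primary: "The primary outcome will be the response rate for CSBM during the treatment period". Patients whose mean weekly CSBM count rises by at least 1 "compared with the last 14 days of the run-in period are defined as responders".
- Secondary: "Secondary outcomes will include the response rate for CSBM during the follow-up period".

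Neither definition sets a minimum length of diary, and neither assigns a status to patients who leave.

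Under Study design, "All three groups then underwent an 8-week treatment and an 8-week follow-up period". The Interventions section gives both study drugs for 8 weeks, so the follow-up period is off drug.

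The section on withdrawal and dropout covers retention and compliance but not the outcome of a patient who leaves. It lists reasons for ending participation: "The trial would be terminated in a specific subject if he/she has: 1) presence of severe adverse effect" is the first. The Sample size calculation expects some loss: "Further, assuming a 15% dropout rate".

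**The concern.** Under ITT, patients who leave stay in the denominator, so the imputation rule decides their responder status. At 15% dropout that is about 0.15 × 291 = 44 patients.

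For the follow-up endpoint, the last observation of someone who never returns a follow-up diary comes from the treatment period. The endpoint asks what remains after the drug is stopped, and these patients would answer it with on-drug data.

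For the primary endpoint, a patient taken out of the trial for a severe adverse effect is scored on whatever diary exists and may be a responder. A short record is also noisier, so chance alone more often produces a mean rise of 1 per week.

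At stake are the claim of lasting benefit and the meaning of a responder in the main result.

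**Working it through.** **1. Follow-up responder rate**

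Inputs from the Background section (earlier placebo-controlled trial): MZRW 43.3% during treatment and 30.0% in follow-up; placebo 8.3% and 15.0%. From the Sample size calculation: 15% dropout, used as the top of a range.

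Let d be the proportion with no follow-up diary. Then

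LOCF rate = (1 − d) × follow-up rate + d × on-treatment rate.

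| d (both arms) | MZRW | Placebo | Difference |
|---|---|---|---|
| 0% | 30.0% | 15.0% | 15.0 |
| 5% | 30.7% | 14.7% | 16.0 |
| 10% | 31.3% | 14.3% | 17.0 |
| 15% | 32.0% | 14.0% | 18.0 |

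For d = 15%: 0.85 × 15.0 + 0.15 × (43.3 − 8.3) = 12.75 + 5.25 = 18.0 points. Both parts of the error point the same way, because the carried MZRW rate is too high and the carried placebo rate too low.

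**2. Primary endpoint: chance response on a short record**

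The document gives no distribution of CSBM counts, so these are assumptions: Poisson counts at a constant rate, no treatment effect, a 14-day run-in restricted to at most 2 per week (the inclusion ceiling), and the week as the carried unit. A patient who leaves after week w has the week-w count carried to weeks w + 1 to 8, so the 8-week total is (sum of weeks 1 to w − 1) + (9 − w) × (week-w count). The patient responds if that total is at least 8 × (run-in mean + 1).

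| Assumed rate per week | Full 8 weeks | Leaves after week 6 | After week 4 | After week 2 |
|---|---|---|---|---|
| 0.5 | 2% | 4% | 7% | 12% |
| 1.0 | 11% | 13% | 17% | 20% |
| 1.5 | 20% | 22% | 25% | 28% |

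**3. Primary endpoint: difference between arms**

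Completers are given the planned rates, MZRW 40% and senna 20%. Dropout by arm and the last status of dropouts are assumed. The non-responder rate is (1 − d) × completer rate.

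| Dropout, MZRW / senna | Last status of dropouts | LOCF difference | Non-responder difference |
|---|---|---|---|
| 15% / 15% | 40% / 20% | 20.0 | 17.0 |
| 15% / 15% | 60% / 30% | 21.5 | 17.0 |
| 15% / 15% | 20% / 20% | 17.0 | 17.0 |
| 20% / 10% | 40% / 20% | 20.0 | 14.0 |
| 10% / 20% | 40% / 20% | 20.0 | 20.0 |
| 10% / 20% | 20% / 20% | 18.0 | 20.0 |

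LOCF can lie above, level with or below the non-responder result.

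**4. Effect of non-responder scoring on power**

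The plan's dropout step reproduces: 82 / 0.85 = 96.5, rounded up to 97; 3 × 97 = 291. With 15% dropout in each arm, 40% and 20% become 0.85 × 40 = 34% and 0.85 × 20 = 17%.

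The power of the chi-square test without continuity correction is Φ{[δ√n − z√(2p̄(1 − p̄))] / √(p₁(1 − p₁) + p₂(1 − p₂))}, with δ = 0.17, n = 97 and p̄ = 0.255. Here √(2 × 0.255 × 0.745) = 0.616 and √(0.2244 + 0.1411) = 0.605.
- Two-sided 0.05: (1.674 − 1.960 × 0.616) / 0.605 = 0.77, power 78.0%.
- Two-sided 0.025: (1.674 − 2.241 × 0.616) / 0.605 = 0.48, power 68.6%.

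For 80% power, 103 or 124 randomised per arm would be needed. Both levels are shown because the stated 82 per arm reproduces at two-sided 0.05, while the stated two-sided 0.025 gives 99. That is a separate matter.

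**The case against.** A reader might infer that LOCF biases the primary comparison towards whichever arm loses more patients to adverse effects. The document does not support that. It gives no dropout by arm, by reason or by last status, and the third table shows that the size and sign turn on these. A patient who leaves for lack of effect carries non-response forward, and one with no post-baseline diary carries zero change.

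Nor does the chance-response figure by itself show a difference between arms, since it applies alike in all of them. At 1 per week and leaving after week 2, 15% dropout adds about 0.15 × (20.1 − 11.3) = 1.3 points to each arm and nothing to the difference. Dropout of 20% against 10% would shift the difference by 0.10 × 8.8 = 0.9 points, against a planned 20.

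The 18.0 points for follow-up are near an upper bound. They need all 15% to be lost with no follow-up diary, equal loss in both arms, on-treatment status equal to the earlier trial's rates, and true off-drug rates equal to the observed ones. The earlier rates may themselves rest on an imputation that the article does not describe. The article also does not say whether the carried unit is a day, a week or a visit.

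Non-responder scoring is no neutral benchmark. It too is a single imputation, so the complaint that LOCF understates uncertainty applies to it as well. On the same follow-up inputs at 15% loss it gives 25.5% − 12.75% = 12.75 points, which is 2.25 below the 15.0, while LOCF is 3.0 above.

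All of this stands, and it limits the claim. It does not remove the defect: the rule is stated without limit, nothing in the article overrides it, and a sensitivity analysis in an unseen analysis plan would not change the rule fixed here.

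**Conclusion.** The point holds, led by the follow-up endpoint. There the rule replaces off-drug outcomes with on-drug ones, and the protocol's own earlier-trial rates give the direction: it favours MZRW over placebo by about 1 to 3 points on a difference of 15.0, for 5% to 15% lost before follow-up, under the equal-loss and carried-rate assumptions above.

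For the primary endpoint, the finding is narrower. LOCF allows a patient who leaves early, including for a severe adverse effect, to be counted a responder on a short record, and chance response in a no-effect patient is higher on such a record at every rate tried. The effect on the comparison between arms is undetermined. Severity: should be fixed.

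**What to change.** Replace the LOCF sentence with rules by endpoint.
- Follow-up responder rate: carry no treatment-period data into follow-up.
- Both responder endpoints: count patients who leave before the end of the relevant window as non-responders. Add multiple imputation of weekly CSBM counts as a sensitivity analysis, because non-responder scoring is conservative and does not reflect imputation uncertainty.
- Symptom scores: use a mixed model for repeated measures on the observed data, without LOCF.

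The wording and the extra analyses cost little. Trial status reports 20 enrolled and none through treatment at submission, so at that point the change could be made before outcome data were complete for anyone. The real cost is in planning: the expected MZRW–senna difference falls from 20 to 17 points, and the stated 80% power should be restated as about 78% (two-sided 0.05) or about 69% (two-sided 0.025) with 97 per arm, or the sample size revisited.

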### Assignment and blinding

Block randomization was carried out in 1:1:1 ratio according to the sequence generated with Random Allocation Software (Version 1.0.0), Isfahan, Iran. The RA assigns treatments according to the codes that are kept in opaque sealed envelopes with consecutive randomization numbers. Treatment assignments will not be revealed and are blinded to the patients and investigators (including statisticians) until the entire study is completed. At the last visit, all patients and the PI/RAs will complete a questionnaire about which treatment (CHM group, WM group or placebo group) the patients received to evaluate the success of blinding. Code breaks should only occur in exceptional circumstances when knowledge of the actual treatment is absolutely essential for further management of the patient.

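### The analysis section tests at two-sided 0.05 while the sample size section relies on 0.025 to hold the overall level at 5%, and the 82 per arm fits only 0.05

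*Protocol article*

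**What the plan says.** The Sample size calculation assumes "response rates for TCM, senna and placebo were 40%, 20% and 10%, respectively". It uses a "two-sided Chi-square test without continuity correction" "at a significance level of 0.025 (used to maintain the overall significance level at 5" per cent). From this it concludes that "82 patients per treatment group were deemed sufficient to achieve 80% power in detecting treatment differences" and, "assuming a 15% dropout rate", arrives at "a total of 291 patients (97 per arm").

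The Statistical analysis section opens by covering all efficacy and safety analyses and then states: "The statistical significance is defined as two-sided *P* value of <0.05". It makes no exception for the primary outcome and gives no adjustment, no testing order and no rule that an overall three-arm test must be significant first.

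The Outcomes section names a single primary outcome, the CSBM response rate over the treatment period. The Background gives the aim as comparing MZRW with senna and with placebo, so the aim contains two comparisons that share the MZRW arm. Allocation is equal: "Block randomization was carried out in 1:1:1 ratio".

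**The concern.** The authors saw that two comparisons on one primary outcome need a stricter level per test. They named that level when sizing the trial, then wrote an analysis rule without it. Three things are at stake.

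- **The error claim.** With both comparisons at 0.05, the overall 5% level in the Sample size calculation is not kept.
- **The verdict on the trial.** A result with P between 0.025 and 0.05 is a success by one section and a failure by the other. For example, 28/82 responders against 16/82 gives P = 0.034.
- **The power claim.** If 0.025 really governs, the sample size should follow from 0.025. It does not.

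**Working it through.** **Inputs.** Response rates 40% (MZRW), 20% (senna) and 10% (placebo); 80% power; two-sided chi-square test without continuity correction; 0.025 per test; 82 evaluable and 97 recruited per arm; 15% dropout (all from the Sample size calculation). Threshold 0.05 (Statistical analysis). Equal arms (Assignment and blinding).

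**1. Reproducing 82 per arm.** The binding comparison in the aim is 40% vs 20%. With p̄ = 0.30,

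n = [z(1−α/2)·√(2·p̄·(1−p̄)) + z(0.80)·√(p₁(1−p₁) + p₂(1−p₂))]² / (p₁−p₂)²

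Here √0.42 = 0.6481, √(0.24 + 0.16) = 0.6325 and z(0.80) = 0.8416.

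- Two-sided 0.05: (1.960 × 0.6481 + 0.8416 × 0.6325)² / 0.04 = 1.8025² / 0.04 = 81.2, so **82**. This is the plan's figure.
- Two-sided 0.025: (2.241 × 0.6481 + 0.8416 × 0.6325)² / 0.04 = 1.9849² / 0.04 = 98.5, so **99**.

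The dropout step is sound: 82 / 0.85 = 96.5, so 97 per arm and 3 × 97 = 291. At 0.025 it would be 99 / 0.85 = 116.5, so 117 per arm and 3 × 117 = 351. Other formulas do not rescue 82 at two-sided 0.025: unpooled variance gives 96, arcsine 98, and continuity correction 109. One-sided 0.025 does give 82, but that is the same test as two-sided 0.05 and adjusts for nothing.

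**2. Power with the planned numbers.** Power = Φ{[(p₁−p₂)√n − z(1−α/2)·√(2p̄(1−p̄))] / √(p₁(1−p₁) + p₂(1−p₂))}. For 40% vs 20% at n = 82 and 0.025: (1.8111 − 1.4526) / 0.6325 = 0.567, and Φ(0.567) = 71.5%.

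| Comparison | n per arm | at 0.05 | at 0.025 |
|---|---|---|---|
| 40% vs 20% | 82 | 80.4% | 71.5% |
| 40% vs 20% | 97 | 86.6% | 79.3% |
| 40% vs 10% | 82 | 99.6% | 99.0% |

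Under the design assumptions, the chance that MZRW vs senna lands between the two thresholds is 80.4 − 71.5 = about 9 percentage points.

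**3. Family-wise error for the two comparisons in the aim.** Take all three arms as equal and let v be the variance of one arm's estimate. The two differences share the MZRW arm, so their covariance is v and each has variance 2v. Their correlation is 0.5. The error is 1 − P(|Z₁| < c and |Z₂| < c):

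- each at 0.05 (c = 1.960): **9.1%** (9.75% if independent; Bonferroni bound 10%);
- each at 0.025 (c = 2.241): **4.6%** (4.9% if independent).

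Simulated chi-square tests, one million trials per setting at 82 and 97 per arm and common response rates of 10%, 20% and 40%, give 8.6% to 9.4% with each test at 0.05.

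**4. Fixed sequence at 0.05.** If MZRW equals placebo, any error in the family requires rejecting that first hypothesis, which happens at most 5% of the time. If MZRW differs from placebo, only MZRW vs senna can be a false positive, again at most 5%. The chance of passing both steps is at least 80.4 + 99.6 − 100 = 80.0% at 82 per arm.

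**The case against.** The best defence is that the 0.05 sentence sits among general remarks on software and baseline tables. On that view it means the general or overall level, and the specific 0.025 statement governs the primary comparisons. That reading is possible, but the text does not say so, and the section declares that it covers all efficacy analyses. It also does not save the plan, because if 0.025 governs, 82 per arm does not give 80% power. A statistical analysis plan that is not shown could settle the matter only by overriding one of two numbers printed here.

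A second defence is that 9% is a worst case. This stands. It holds when all three arms are equal. The team's earlier trial reported response rates of 43.3% vs 8.3% for MZRW and placebo; if MZRW truly beats placebo, only MZRW vs senna can be a false positive, at 5%. A claim to hold the overall level must nevertheless cover the worst case.

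A reader might go further and infer that three arms mean three pairwise tests, giving 12.2% at 0.05 and 6.4% even at 0.025, or that the plan never indicates which two comparisons matter. The documents do not support this. The stated aim is MZRW against senna and against placebo, which matches a level of 0.05/2, and senna vs placebo is not given as an aim.

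Finally, fixed-sequence testing is one valid choice among several. Holm would also control the error, with power for MZRW vs senna of at least 99.0 + 80.4 − 100 = 79.4% at 82 per arm.

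**Conclusion.** The contradiction is real and should be resolved before unblinding. As written, the plan does not secure the 5% overall level it claims: with the two comparisons of the aim each at 0.05, the family-wise error is up to about 9%, under equality of all three arms and equal allocation. It would be wrong to say that the trial's error rate simply is 9%, because the intended role of the 0.05 sentence is unclear and the figure is a maximum.

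The sample size mismatch does not depend on that reading. Under the plan's own assumptions, 82 per arm corresponds to two-sided 0.05, and at the stated 0.025 the power for MZRW vs senna is about 71.5%. If all 97 recruited per arm are analysed and the assumed rates still hold, it is 79.3%. MZRW vs placebo is well powered at either level.

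**What to change.** **Statistical analysis section.** Name the confirmatory tests on the treatment-period CSBM responder rate as a fixed sequence: MZRW vs placebo first, then MZRW vs senna, each at two-sided 0.05, the second being confirmatory only if the first is significant.

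**Sample size calculation.** Replace the 0.025 statement with this rule. The figures 82, 97 and 291 then stand, with about 80% power for 40% vs 20%.

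**Cost.** A few sentences and no extra patients. Senna vs placebo carries no confirmatory claim, and MZRW vs senna carries none if the first test fails. At submission the Trial status section reports 20 subjects enrolled and none through treatment, so the rule could then be fixed without knowledge of results.

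**Alternative.** If 0.025 per comparison is kept, state it in both sections and restate the power for MZRW vs senna as about 71.5% with 82 evaluable per arm. Restoring 80% needs 99 evaluable per arm, which is 117 recruited per arm and 351 in total after 15% dropout: 60 more than planned. Writing 0.025 into the analysis section without restating the power would leave the 80% claim wrong.
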